**Fig. 2 Fig2:**
[figure not shown]
Data collection schedule

### Adverse events

There will be a vigilant surveillance system in place for adverse events (AEs) occurring during the course of the trial with particular emphasis on identifying, recording, reporting and managing serious suspected drug reactions. We will use standard definitions to distinguish between an adverse event (AE), a serious adverse event (SAE) and a serious suspected adverse drug reaction (SSARD).

In the event of any AE reported by the participant, their attendant or health care staff, the research assistant will complete an AE Form, which will include any available medical diagnosis. For reporting SAEs, a form will be provided by Pfizer known as a Pfizer-provided Investigator-initiated Research Serious Adverse Event Form. The Reportable Event Fax Cover Sheet provided by Pfizer will also be included with each SAE submitted. The research assistant will photocopy and complete this form, send it in the post to the central research office and call the trial manager on the same day providing a verbal report of the event. The research assistant will be trained to differentiate between AEs and SAEs. However, the trial manager, who is medically qualified, will ensure that the event is classified appropriately after receiving the verbal report. The trial manager will also code the event using the Medical Dictionary for Regulatory Activities (MedDRA) [18] and cascade the information as follows.

All AEs must be reported to the principal investigator (Pakistan) within 3 days of detection. AE data will be collated and reported to the trial sponsors and National Bioethics Committee at 6-monthly intervals. These must also be reported to the Study Operational Committee and the Independent Trial Steering Committee at their regular meeting. All AEs that have the potential to develop into SAEs will be followed to resolution or stabilization and reported as SAEs if they become serious. All SAEs must be reported to the principal investigator and Pfizer within 24 h of detection and should also be reported to the trial sponsors and the National Bioethics Committee within three working days. All SSARDs should be reported to the sponsors and the committee within 24 h of the event. All serious events must also be reported to all study investigators and the chair of the Independent Trial Steering Committee (within 3 days for SAEs and within 24 h for SSARDs). If the trial manager requires more detail in relation to any SAEs or SSARDs then they may request the trial statistician to unblind the treatment condition. The chief investigator will have the overall responsibility to ensure that all AEs are reported according to the above protocol.

In addition to assessing seriousness, the trial manager, who is medically qualified, will assess all AE for causality, severity and expectedness. This will be done in consultation with the principal investigator and the event will be classified as follows:Unrelated: when the event is considered not related to the study treatmentPossibly: when an association of the event with the study treatment cannot be ruled outProbably: when temporal association and an absence of any other explanation suggest that the event could be related to the study treatmentDefinitely: based either on known side effects of the study treatment or on challenge testing, a suggestion that the study treatment is the most likely cause of the event

All AEs/SAEs that fall under the possible, probable or definitive category will be classified as adverse reactions or SSADRs.

The trial manager can make the following assessment based on severity, which should not be confused with seriousness (a statutory definition) differentiating between AEs and SAEs:Mild: these events cause minimal discomfort, are easily tolerated and do not interfere with routine life activitiesModerate: these events cause moderate discomfort and do interfere with routine life activitiesSevere: these events cause much discomfort and lead participants to stop their routine life activities

If the event is judged to be an adverse reaction, serious or otherwise, this must be judged on expectedness based on what is already known on the safety profile of the drug under study. Each participating hospital site will have a named medical practitioner who will be responsible for dealing with any AE that requires medical attention. All medical expenses resulting from such events will be covered by the trial budget. This will not include any elective procedures, operations or admissions planned prior to participating in the trial. In addition to collecting detailed clinical information on the AE Form, other relevant medical information will be collected from hospital. These events will be followed up till resolution or returning to a stable medical state. We will not expect any events that occur after the completion of follow-up to be relevant to the trial and, therefore, no active surveillance will continue beyond trial completion. Nevertheless, any event reported to the trial manger will be recorded and kept in the records along with other trial data.

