#### Randomization and allocation

Those who consent will be randomly assigned to one of the two treatment conditions by using a computer-generated allocation sequence designed at the University of York. The system, created in software R v3.2.2, will generate a permuted block randomization list for each site with stratification factors including gender and concomitant smoking. Based on this random sequence, the system will allocate each newly recruited participant either to varenicline or to placebo treatment. For treatment allocation, the research assistant will make a phone call to the trial manager based at the central research office in Islamabad. On providing the basic information on recruiting district, gender, and concomitant smoking, the trial manager will generate a trial ID by running a prespecified code (for each random block) in the R file. At this point, both the trial manager and the research assistant will be unaware of the treatment condition associated with each trial ID. The trial ID will correspond to that on the medication packs already made available at each participating hospital. Under no circumstances will an enrolled participant be dispensed a medication pack other than the one assigned through the randomization system. To ensure double-blinding, we will use identical medication packs for both placebo and varenicline, labeled only with a unique trial ID. The investigators, research assistants and participants will be blinded to the allocation until the trial database is locked at the end of the study.

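### For serious adverse events, the trial manager who grades causality may be given the treatment code before the grade is recorded, so the drug-reaction label is open to knowledge of the arm

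*Protocol article*

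**What the plan says.** All of this is in the protocol article.

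**Code break (Adverse events).** Where the trial manager needs further information on a serious event, the rule is that "they may request the trial statistician to unblind the treatment condition". The trigger is a wish for more information, the recipient is the trial manager, and the scope is SAEs and SSARDs.

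**Grading (Adverse events).** The section says that "the trial manager, who is medically qualified, will assess all AE for causality, severity and expectedness", and adds: "This will be done in consultation with the principal investigator". It also has the trial manager check that an event is correctly classed as serious or not, and code it in MedDRA.

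**What the grade decides (Adverse events).** "All AEs/SAEs that fall under the possible, probable or definitive category will be classified as adverse reactions or SSADRs". On timing, "All SSARDs should be reported to the sponsors and the committee within 24 h of the event".

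**Allocation and blinding (Randomization and allocation).** When a participant is allocated, "the trial manager will generate a trial ID by running a prespecified code (for each random block) in the R file", and at that moment "both the trial manager and the research assistant will be unaware of the treatment condition associated with each trial ID". A later sentence keeps investigators, research assistants and participants blind up to database lock. It does not name the trial manager and gives no exception for code breaks.

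**The concern.** Breaking the code for a serious event is ordinary practice. The difficulty is who receives the code here, and that no point in the sequence is fixed for it. Knowing the arm adds little to the description of an event; it mainly informs the judgement of whether the study drug caused it, and that judgement belongs to the person who receives the code. A grader who knows that the participant took placebo will lean towards calling the event unrelated. One who knows that the participant took varenicline will find it hard to rule the drug out.

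At stake are the recorded profile of drug reactions and the speed at which serious events reach the sponsors, the ethics committee, the investigators and the steering committee chair. The article presents the trial as the first randomized test of a drug for stopping waterpipe smoking, so its reaction data are likely to be read closely.

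**Working it through.** The plan gives no figure on this point, so the check sets its statements side by side.

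1. **Is the grader the person who may be unblinded?** Yes. Both statements in the Adverse events section name the trial manager.

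2. **Which events are covered?** SAEs and SSARDs only. No route to the code exists for a non-serious event.

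3. **Can the break precede the grade?**
   - *SSARD:* by the article's own definition this is a serious event already graded possible or higher. The causality judgement has been made before the clause applies to the event under that label.
   - *SAE not yet graded:* the clause applies to any SAE. The text neither requires the grade first nor says that the break comes first. The order is open, and this is where the gap lies.

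4. **Does consultation close the gap?** Only in part. If the principal investigator stays blind, there is a blind second opinion, but the lead assessor may know the arm. If the principal investigator learns the arm during the consultation, the until-lock blinding of investigators is broken. The article does not say which is intended.

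5. **What changes with the grade?** Take one serious event under each grade:
   - *Graded unrelated (stays an SAE):* sponsors and National Bioethics Committee within three working days; all investigators and the steering committee chair within 3 days.
   - *Graded possible, probable or definite (becomes an SSARD):* all of these within 24 h.
   - *Unchanged either way:* the principal investigator and the drug supplier are told of every SAE within 24 h of detection.

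   The grade therefore decides the label and four of the six reporting lines.

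6. **Does the knowledge last?** Participants withdrawn from treatment remain in follow-up (Study participants). After a break, the manager knows that participant's arm when grading any later event in the same person, including a non-serious one.

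7. **Which planned results use the grade?** The Statistical analysis section compares AEs and SAEs by arm with chi-square tests and does not mention causality class. The primary outcome is self-report verified by carbon monoxide, with cotinine where needed. Neither depends on the causality grade.

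8. **How many events?** The article states no expected number of SAEs or code breaks. Without one, no count or percentage of affected grades can be derived.

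**The case against.** The strongest reply is that this is a condensed article. Sign-off, logging and release criteria usually sit in the full protocol, and the Discussion says that a policy on managing SAEs will be written. The manager also cannot self-unblind but must ask the statistician, and a second person is consulted on causality. All of that stands, and the absence of a log or sign-off form would be no finding by itself. But the article does more than omit detail. It states a rule, with a loose trigger and with the grader as recipient, and that stated rule is what needs changing.

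Four stronger readings are tempting, and the documents do not support them.

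- **The manager is unblinded before judging every adverse event.** The clause is limited to serious events, is optional, and leaves the order open.
- **The article contradicts itself on the manager's blinding.** The statement that the manager is unaware applies at the moment of allocation, and the until-lock sentence does not name the manager. What needs reconciling is the position of the principal investigator.
- **Allocation concealment is compromised.** The manager does run the block-wise code, so a break says something about others in the same block. But research assistants decide eligibility, consent comes before the allocation call, IDs come from a preset sequence, and only the assigned pack may be dispensed. Bias would require information to reach a site while that block was still filling. Any percentage would need a block size, which the article does not give. It would measure how well a block-mate's arm could be guessed, not bias in a result. At most this is a secondary reason to keep the person issuing IDs blind.
- **The trial's comparisons are biased.** Neither the primary outcome nor the planned AE and SAE tests use causality class.

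**Conclusion.** The point holds in a limited form. For a serious event not yet graded, the stated rule lets the person who leads the causality judgement learn the arm first, on no firmer ground than wanting more information. What is exposed is the causality and expectedness grading of such events, the reaction or SSARD label that follows, and the step from a three-day to a 24 h reporting route. Later events in an unblinded participant are exposed in the same way. No efficacy result and no stated between-arm test is affected.

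The number of affected events is unknown and could be small. The conclusion assumes that no document outside the article already requires a blind grade before a break. If one does, the article's clause needs only to be brought into line with it. The change is still worth making, because it corrects a stated rule at little cost.

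**What to change.** In **Adverse events**:

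- Require seriousness, causality, severity and expectedness to be recorded blind, with date and time, before any code break. A later reassessment may be added but must not overwrite the blind grade.
- State the criterion for a break in place of the present open wording.
- Have the statistician release the code, where it is needed, to someone already in the trial who does not grade events, allocate or meet participants. The steering committee chair, who already receives every serious event, is one example. The site's named medical practitioner is a poor choice because it would move knowledge of the arm to a clinician in contact with participants.
- Log each break, with its time, reason and recipient.

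In **Randomization and allocation**, state how the until-lock blinding of investigators is kept when the principal investigator is consulted on causality, and add the trial manager to those kept blind.

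The cost is protocol and procedure wording, using existing staff. The downside is an extra step when the treatment must be known, and that step has to fit within the 24 h reporting window. The article does not say whether the clause is also meant for code breaks needed for a participant's care. The team should state this so that the new wording takes account of it.

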### Sample size

The primary outcome of the study is continuous abstinence for at least 6 months between week 5 and week 25. Our previous data from a clustered randomized trial in 33 centers in Pakistan [13] with 1955 participants gave an estimate of 37% continuous abstinence at 25 weeks for the behavioral support arm of the trial. A difference of an additional 13 percentage points in the varenicline group is the minimum clinically important difference that we are interested in detecting; this is the median difference reported by the trials which looked at the effectiveness of varenicline and were included in the systematic review by Cahill et al. [8]. In order to detect an absolute difference of 13% in the varenicline plus behavioral support versus the placebo plus behavioral support group, with 80% power and 5% significance, 228 patients would be required per arm. Allowing for a 10% dropout, a total of 508 patients will, therefore, need to be recruited into the study.

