**Methods/design:**

This is a two-arm, double-blind, placebo-controlled randomized trial conducted in four districts in Punjab, Pakistan. Study participants include adults using a waterpipe (with or without concomitant cigarette, bidi or other forms of tobacco smoking) on a daily basis for at least 6 months and who are willing to quit. We will individually randomize 510 participants to one of the two arms of the trial. Participants in the intervention arm will receive varenicline and behavioral support and those in the control arm will receive placebo and behavioral support. The primary outcome will be continuous abstinence for at least 6 months (week 25) which is biochemically verified by a carbon monoxide level of <10 ppm. Secondary outcomes will include biochemically verified 7-day point abstinence at 5, 12 and 25 weeks and any lapses and relapses between the different assessment points. Tertiary outcomes will include assessment of withdrawal symptoms using the Mood and Physical Symptoms Scale (MPSS), smoking dependency using the Lebanon Waterpipe Dependency Scale (LWDS-11) and monitoring adverse outcomes.

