### Behavioral support

Behavioral support will be offered to all waterpipe tobacco smokers as part of routine care. Hence, all trial participants, irrespective of their treatment condition, will receive behavioral support intervention using an educational flipbook. This will consist of two structured sessions. A 30-min session at the first visit will aim to encouraging waterpipe tobacco smokers to see themselves as nonusers and to set a plan for a quit day 1 week later. This is then followed by a 10-min session, coinciding with their quit day, to review progress. Further encouragement and support will be offered at subsequent visits in week 5.

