### Varenicline

Participants allocated to the varenicline and behavioral support arm will receive their first week’s supply on the day of trial enrollment. The treatment, in the form of 0.5-mg tablets, will be dosed at 0.5 mg once daily on days 1–3 and 0.5 mg twice daily on days 4–7. Participants will be expected to return at the end of week 1, coinciding with their quit day, at which point they will be dispensed another pack of medication for 11 weeks, with the pill in the form of 1-mg tablets to be taken twice daily for the rest of the treatment duration. Adherence will be monitored at each visit by using a 7-day timeline follow-back and by looking at the tablets left in the bottle. A 7-day timeline follow-back will consist of a set of questions administered at weeks 1, 5 and 12 asking participants if they have taken the prescribed treatment in the previous week by recalling each day of the week. Adherence will be considered “complete” if the participant adheres throughout 12 weeks; and “partial” if adherence is either irregular or not for the entire period. Participants will be asked to record the nature, timing and duration of any adverse events (AEs) with clear guidance on when to stop the medication and when, and how, to report back to the named clinician in the participating hospital. These clinicians would have received the basic training required in this regard.

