### Primary outcome

As per Russell’s Standard [16], the primary outcome will be self-reported continuous abstinence for at least 6 months (no smoking allowed in the 7 days prior to each of the three assessments) which is biochemically verified by a carbon monoxide (CO) level of <10 ppm measured by Micro CO (Micro Medical Ltd., Rochester, United Kingdom) at week 5, week 12 and week 25. When a participant self-reports abstinence with an elevated CO level of >10 ppm on any of the three assessments, we will use urinary kits for checking cotinine levels in such cases. Depending on the cotinine level findings the participant will be categorized as a smoker or not.

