### Secondary outcomes

Based on the combination of self-report and CO levels, these will include:Point abstinence, defined as a self-report of not smoking in the previous 7 days and verified by a CO level of <10 ppm, at week 5, week 12 and week 25Early lapse, defined by a self-report of smoking (even once) after the quit date but having point abstinence at week 5Late lapse, defined by a self-report of smoking (even once) between week 5 and week 12 but showing point abstinence at week 5 and week 12Early relapse, defined by point abstinence at week 5 but a smoking status in later assessmentsLate relapse, defined by point abstinence at week 5 and week 12 but a smoking status at week 25Differences in the point and continuous abstinences, lapses and relapses between exclusive waterpipe smokers and those who combine it with other forms of smoking tobacco

We will also translate the MPSS [17] for use in a Pakistani population. Once translated, the scale will be administered at baseline and week 25. The scale assesses withdrawal symptoms including anxiety, depression, irritability, restlessness, hunger, concentration and sleep. It also assesses the frequency and strength of urges to smoke. As above, we will also translate the LWDS-11, a tobacco-dependence measure [7], to be administered at baseline and week 25. The scale consists of 11 items and four subscales, the first representing nicotine dependence, the second negative reinforcement, the third psychological craving and the fourth positive reinforcement.

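### The primary outcome is labelled continuous abstinence for at least 6 months, but its stated window is 20 weeks and its counting rule, as written, is 7-day abstinence at three visits

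*Protocol article*

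**What the plan says.** The protocol article describes the primary outcome in four places.

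- **Abstract, Methods/design:** "continuous abstinence for at least 6 months (week 25"), which treats 6 months and week 25 as the same thing.
- **Aims and objectives:** the key aim is 6 months of continuous abstinence from every form of tobacco smoking. The primary objective is then put as validated continuous abstinence at week 25.
- **Primary outcome:** "self-reported continuous abstinence for at least 6 months (no smoking allowed in the 7 days prior to each of the three assessments"), verified by CO below 10 ppm at weeks 5, 12 and 25.
- **Sample size:** "The primary outcome of the study is continuous abstinence for at least 6 months between week 5 and week 25".

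Three other sections bear on it.

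- **Behavioral support and Varenicline** fix the quit day. The first session is used to "set a plan for a quit day 1 week later", and "Participants will be expected to return at the end of week 1, coinciding with their quit day".
- **Secondary outcomes** defines point abstinence by the same 7-day self-report and the same CO limit at the same three visits. It defines late lapse as "a self-report of smoking (even once) between week 5 and week 12 but showing point abstinence" at both of those visits.
- **Statistical analysis** lists lapse over weeks 5 to 12, 12 to 25 and 5 to 25 among the binary secondary outcomes.

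**The concern.** There are two linked problems.

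First, the duration and the window in the Sample size section cannot both be right: 20 weeks does not contain at least 6 months. The start of the abstinence period is also unsettled. Sample size starts it at week 5, whereas the 6-month label comes close to fitting only if the period starts near enrolment or the quit day.

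Second, the only counting rule given for continuous abstinence is a set of three 7-day windows. Nothing in that rule excludes someone who smoked between visits, and the protocol's own late-lapse category describes such people. Two analysts could therefore classify the same participant differently, one following the word continuous and the other following the bracket.

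At stake is what the trial may claim. A report of 6 months' continuous abstinence would describe a longer and stricter outcome than the one counted.

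**Working it through.** **1. The plan's own figure.** Inputs from Sample size: 37% against 50% (37 + 13), 80% power, 5% significance (taken as two-sided), 1:1 allocation. Pooled-variance formula without continuity correction:

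n = [1.960 × √(2 × 0.435 × 0.565) + 0.842 × √(0.37 × 0.63 + 0.50 × 0.50)]² / 0.13² = (1.374 + 0.585)² / 0.0169 ≈ 227.1, rounded up to 228 per arm.

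Dropout: 228 / 0.90 = 253.3, rounded up to 254 per arm, so 508 in total. Both stated figures reproduce.

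**2. Duration.** Inputs: visits at weeks 5, 12 and 25; quit day at the end of week 1; 1 month = 30.44 days, so 6 months = 26.1 weeks.

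| Start | Weeks to week 25 | Days | Months |
|---|---|---|---|
| Week 5 (Sample size) | 25 − 5 = 20 | 140 | 4.6 |
| Quit day, end of week 1 | 25 − 1 = 24 | 168 | 5.5 |
| Enrolment | 25 | 175 | 5.7 |

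Every start falls short of 26.1 weeks: by about 6 weeks on the window in Sample size, and by about 2 weeks from the quit day.

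**3. Time covered by the counting rule.**

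- From the quit day: 3 × 7 = 21 of 168 days, 12.5%.
- Within weeks 5 to 25: the week 5 window lies before week 5, so only the week 12 and week 25 windows count. 2 × 7 = 14 of 140 days, 10%. The uncovered time is weeks 5 to 11 (6 weeks) and weeks 12 to 24 (12 weeks): 18 weeks, or 126 days.

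**4. The definitions side by side.** Point abstinence at one visit is no self-reported smoking in the previous 7 days plus CO below 10 ppm. The primary rule asks for the same at weeks 5, 12 and 25, so as written it is point abstinence at all three. Take a participant who smokes once in week 8 and is point abstinent at weeks 5, 12 and 25. This person is a late lapser under Secondary outcomes, passes the primary rule, and has smoked inside the period that Sample size calls continuous.

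**5. Sensitivity, by assumption only.** The documents give no rate of smoking between visits. Suppose a stricter rule lowered both arms' rates by the same proportion:

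| Reduction | Rates | Difference | Risk ratio | Power at 228 per arm |
|---|---|---|---|---|
| 0% | 37.0% v 50.0% | 13.0 points | 1.35 | 80.2% |
| 10% | 33.3% v 45.0% | 11.7 points | 1.35 | 72.7% |
| 20% | 29.6% v 40.0% | 10.4 points | 1.35 | 64.6% |

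If the 13-point difference held at the lower rates instead, power would be 81.2% (10% reduction) and 82.6% (20% reduction). The choice of definition can therefore matter for power, but the direction depends on an assumption that the documents cannot settle.

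**The case against.** The strongest reply is that the phrase about self-reported continuous abstinence may stand for a question about the whole period, with the 7-day rule as a further condition. The section also cites a published abstinence standard, which is not at hand and cannot be used to settle the matter. This reading is possible. However, the article describes no such question, and the bracket reads as the definition. It would be going too far to say that lapsers will certainly be counted as successes. What the text supports is that the rule, as written, admits them.

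Other parts of the reply stand:

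- A reader might infer that nobody will be asked about smoking between weeks 12 and 25. Statistical analysis already plans lapse over weeks 12 to 25 and 5 to 25, and changes in smoking pattern are recorded at each follow-up. The gap is that the success rule does not use this information and that Secondary outcomes does not define a week 12 to 25 lapse.
- A reader might cite early lapse as further evidence. On a week 5 to 25 period, smoking before week 5 lies outside it, so only late lapse makes the case.
- A reader might conclude that no participant can ever succeed. The three visits are fixed and the 24-week span from the quit day is often loosely called 6 months, so that shortfall is minor. The 20-week window is the real contradiction.
- The 7-day rule is stated openly and applies equally to both arms under double-blinding.

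**Conclusion.** The point holds and should be fixed. The primary outcome is stated inconsistently: a duration of at least 6 months is placed in a 20-week window (140 days, 4.6 months), and the only counting rule given is 7-day abstinence at three visits, covering 10% of weeks 5 to 25 or 12.5% of the time from the quit day. A late lapser who is abstinent at week 25 meets that rule. This rests on reading the bracket as the definition, which is the natural reading but not the only possible one.

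A reader might infer that the trial is underpowered or its comparison biased. The documents do not support either. The sample size reproduces, no mechanism favouring one arm is shown, and a proportional fall in both arms would leave the risk ratio at 1.35. Whether the 37% control rate was measured under the same rule is not stated, so that remains an open question rather than an error. The consequence is confined to what the result may be called and which participants count as successes.

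**What to change.** Before unblinding, use one definition in the Abstract, Aims and objectives, Primary outcome and Sample size sections. State when the abstinence period starts, its length in weeks, and whether smoking between visits disqualifies. Then choose one of two routes:

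1. **Rename.** Call the outcome *biochemically verified 7-day abstinence at all of weeks 5, 12 and 25*, and drop the words continuous and at least 6 months.
2. **Keep continuous.** Also require no self-reported smoking between assessments from week 5 to week 25. Use the lapse data that Statistical analysis already plans for weeks 5 to 12, 12 to 25 and 5 to 25, and add the missing week 12 to 25 lapse definition to Secondary outcomes.

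Report the definition not chosen as a prespecified sensitivity analysis.

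The cost is mainly wording, because the lapse analyses are already planned. The price is a less favourable label under route 1, or lower abstinence rates in both arms under route 2. Under route 2, the 37% and 13-point assumptions should be checked against the stricter definition.
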